### Randomisation, allocation and masking

Randomisation by means of a stratified block randomisation procedure will be performed by an independent statistician. Participants will be allocated in a 1:1:1 ratio to the three groups. The size of the randomisation blocks is three. Participants will be stratified according to their baseline habitual protein intake (<0.9 or 0.9–1.0 g/kg aBW/day) and sex to ensure homogeneous distribution of baseline habitual protein intake and sex in the three groups across the two recruitment sites, because there may be a different intervention effect by baseline habitual protein or sex. In case couples are eligible, we will allocate them to the same intervention group to limit interference between intervention groups. We will randomly select on which partner the randomisation for the intervention group is based. Any resulting unbalance in the number of subjects per treatment arm will be corrected in the randomisation of the next block. Due to the nature of the study, researchers, nutritionists and participants are not blinded to the study group.

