### Sample size and statistical analyses

#### Sample size

The study is powered to detect a substantial meaningful change of 28 s (SD=61 s)^69^ between the respective intervention groups and the control group on the primary outcome walk time on the 400 m walk test, assuming a two-sided test at α=0.05 with a power of 0.8. For this, 75 participants per group are needed, which is 225 in total. Assuming a drop-out of 15% (which was reported in a comparable study of Bhasin *et al*,^19^ the total number of study participants to be included in the study is n=264. Therefore, we aim to include a total of n=132 at each study site (n=44 per study group per study site).

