#### Persuasive technology study

The primary aim of this study is to examine the effect of persuasive technology on adherence to the personalised dietary advice aiming at increasing protein intake to at least 1.2 g/kg aBW/day in a subsample of Dutch participants from intervention group 1 (n=24) and intervention group 2 (n=24), that is, the first 24 participants of intervention group 1 and the first 24 participants of intervention group 2 that consent to it (written informed consent will be signed).

Participants will be provided with a food storage box that registers which provided protein-enriched food products are taken out. The food box is used to store the protein-enriched food products provided by the research team. Participants will also receive a tablet that allows participants to register any consumed protein-enriched food products and supports them in finding alternative food products that contain a comparable amount of protein. For this, the system uses the personalised dietary advice as provided by the nutritionist and data from the storage box. The tablet application aims to stimulate adherence to the dietary advice by providing tailored and personalised messages. In addition, personality characteristics and communication style preferences that are determined via a questionnaire completed at baseline are used to tailor the style and tone of these messages.^72^

In addition to the personalised messages, half of the participants from intervention groups 1 and 2 who participate in the persuasive technology substudy will also receive a gamified version of the tablet application (n=12+n=12). In this version, participants can earn game points by registering their consumed protein-(en)rich(ed) food products and by playing mini-games about the protein content of foods (ie, guess the protein content, more-or-less protein). The distribution of receiving the gamified version versus standard version is quasi-randomised, where we will balance the group size.

At the consultation meeting, participants receive their food storage box and tablet. Both are fully configured, that is, they are loaded with their personal dietary advice. After the 6-month follow-up visit, participants will be asked to return the equipment and fill out questions on the feasibility and user experience of the provided persuasive technology.

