The secondary objectives are (1) to investigate to what extent participants perceive messages of which the style and tone are adapted to their personal characteristics as personalised and adequate, and (2) to determine the effect of gamification on the effectiveness and feasibility of the persuasive technology.

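### The gamified and standard tablet versions are allocated by an unspecified quasi-random rule, although a secondary substudy objective is to determine the effect of gamification

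*Protocol article*

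**What the plan says.** The protocol article, under Ancillary studies, Persuasive technology study, enrols a Dutch subsample: "the first 24 participants of intervention group 1 and the first 24 participants of intervention group 2 that consent to it". All of them receive a food storage box and a tablet with personalised messages. Half "will also receive a gamified version of the tablet application (n=12+n=12"). The allocation method is given in one sentence: "The distribution of receiving the gamified version versus standard version is quasi-randomised, where we will balance the group size".

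The same section lists, as the second of two secondary objectives, "to determine the effect of gamification on the effectiveness and feasibility of the persuasive technology".

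For the main trial, the section Randomisation, allocation and masking describes a different method: "Randomisation by means of a stratified block randomisation procedure will be performed by an independent statistician". That description concerns the three study groups, and nothing extends it to the tablet version. The same section states that "researchers, nutritionists and participants are not blinded to the study group".

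**The concern.** Quasi-randomised, in its usual meaning, describes a rule that is not truly random, such as alternation or assignment by order of arrival. The article therefore states a weaker method; it does not merely leave a detail to a fuller document. The comparison that depends on it could have been randomised without difficulty. Both versions go to people who have consented to the same substudy, so each has a concurrent comparator, and the trial already has a statistician who produces allocation lists.

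At stake is how a difference between the two versions may be read. If someone can foresee which version comes next and can influence who is entered or when, or if someone can choose the version for a given person, the two sets of 24 may differ in ways that also affect adherence. A difference in adherence could then not be attributed to gamification with the confidence that the wording of the objective implies. With 24 against 24, even a modest imbalance matters.

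**Working it through.** **1. The plan's own figure.** The substudy has 24 + 24 = 48 participants. Half of each 24 is 12, so 12 + 12 = 24 receive the gamified version and 24 the standard one. The stated split reproduces.

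**2. What is fixed and what is not.**
- Stated: the term quasi-randomised, equal group sizes, entry in order of consent, a tablet received fully configured at the consultation meeting, and a causal secondary objective.
- Not stated: the rule, who applies it, whether that person sees participants' questionnaire answers, and whether substudy consent comes before the version is assigned.

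**3. Predictability under assumed rules.** Because the rule is not given, this is a range over candidates. Take one intervention group (24 assignments, 12 of each version) and an observer who knows all past assignments, guesses whichever version is behind, and tosses a coin when they are level.

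For a random block of 2m with m of each version, the expected number of correct guesses is

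m + (2^(2m) / C(2m, m) − 1) / 2.

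- One random block of 24 (m = 12): 2^24 = 16,777,216 and C(24,12) = 2,704,156, with ratio 6.204. Correct guesses: 12 + (6.204 − 1)/2 = 14.6 of 24, or 61%.
- Random blocks of 4 (m = 2): 2 + (16/6 − 1)/2 = 2.833 per block; times 6 blocks = 17.0 of 24, or 71%.
- Random blocks of 2 (m = 1): 1 + (4/2 − 1)/2 = 1.5 per block; times 12 blocks = 18 of 24, or 75%.
- Next person to the smaller group, coin toss when level: every second assignment is certain and the others are even chances, so (12 × 1 + 12 × 0.5)/24 = 75%.
- Alternation with the rule known: 23 of 24 (96%) if the first is unknown and guessed wrongly, 24 of 24 (100%) if it is known.
- Unrestricted randomisation, for reference: 12 of 24, or 50%.

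A simulation of 50,000 sequences for each of the three random-block cases gives the same values (14.6, 17.0 and 18.0). Under any rule with a fixed 12:12 total, the last assignment in each group is determined.

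**4. What these figures do not give.** They say how often the next version could be guessed. Turning that into bias would require knowing how far entry or assignment was influenced and how strongly the influenced characteristic relates to adherence. The article gives neither.

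**The case against.** **Inference beyond the text.** A reader might infer that staff can in fact foresee or choose the version. The article does not say so. Its statement on blinding concerns the study group, not the tablet version. It does not say who configures or hands over the tablets, or that this person sees the personality and communication-style questionnaire; those answers are said only to shape the style and tone of messages. This objection stands, and the concern is conditional for that reason.

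**Predictability is not steering.** Under a mechanical rule such as alternation nobody chooses the version, so bias needs control over who enters or in what order. Entry is limited to the first consenting participants, and both versions come with the same box, tablet and messages, which leaves less reason to refuse or defer. Moreover, the 75% for the smaller-group rule equals that for genuinely random blocks of two, so predictability alone does not separate quasi-randomisation from tight blocking. All this is fair. It does not remove the risk, because the order of consent and assignment is not stated and the unspecified rule may leave discretion.

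**A large bias figure.** A reader might calculate one by supposing that the more and less motivated halves were fully separated. The halves of a normal distribution differ by 1.6 SD, and multiplying by an assumed motivation-adherence correlation of 0.2 to 0.5 gives 0.32 to 0.80 SD. Full separation and the correlation are both assumptions, and the guess rates do not enter the sum. The document does not support such a figure.

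**Small stakes.** This is one secondary objective of one ancillary study at one site. The standard error of a 24 versus 24 difference is √(2/24) = 0.29 SD, so even perfect randomisation would give 80% power at two-sided 5% only for about (1.96 + 0.84) × 0.289 = 0.81 SD. The objective also covers feasibility, to which the adherence argument does not directly apply, and the article openly calls the split quasi-randomised. This stands and limits the weight of the point.

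**Conclusion.** The point holds as a minor design weakness. The article sets an objective in causal terms and rests it on an allocation that it describes as not fully random, by a rule and a person it does not name. If that rule is foreseeable or discretionary, the gamified-versus-standard comparison is open to selection bias. Depending on the rule assumed, and given knowledge of past assignments, between about 61% and 100% of assignments could be guessed. No bias estimate follows from this.

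A reader might also infer that the trial's main results are compromised. They are not: the version is assigned within the intervention groups, after the three-group randomisation, and how it is assigned affects neither that randomisation nor the comparison of 400 m walk time with control. The consequence is confined to the 24 versus 24 comparison at the Dutch site.

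**What to change.** Replace the allocation sentence in the Persuasive technology study section with wording to this effect: within each intervention group, the 24 substudy participants are randomly assigned 1:1 to the gamified or standard version from a concealed list generated by the independent statistician, with each assignment released only after substudy consent and before the tablet is configured. Analyse gamified versus standard with intervention group as a covariate.

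This keeps the 12:12 split, since equal group sizes do not need a quasi-random rule. Some predictability remains with any fixed 12:12 total, but concealment and release after consent leave little opportunity to act on it.

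If allocation has already taken place, state the rule that was used, report the comparison as exploratory and non-randomised, and soften the causal wording of the second secondary objective.

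The cost is one additional allocation list covering 48 people, from a statistician already engaged. No participants, visits or measurements are added. The reporting alternative costs only a change of wording.

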#### Microbiota study

In the microbiota study, the effect of personalised dietary advice aiming at increasing protein intake in community-dwelling older adults with lower habitual protein intake on both the oral and gut microbiota is investigated. The study will be conducted at both study sites.

The human microbiota consists of the 4*10^13^ microorganisms that inhabit the body.^73^ The emergence of next generation DNA sequencing techniques at the start of the 21st century has allowed more detailed study of the microbiota and since then, the microbiota composition has been associated with both health and disease,^74^ as well as ageing itself.^75 76^ Moreover, several interventional studies proved that dietary changes also affect the gut microbiota, with the first microbial shifts being evident within 48 hours.^77^ The altered microbiota in turn, can differentially affect the human host metabolism through the production of metabolically active metabolites. Less is known about the oral microbiota. It was found to be associated with oral health and function and even nutritional status,^78 79^ but its possible role in undernutrition in older adults has not been investigated.

A fresh frozen faecal sample and tongue swab are collected at baseline and 6-month follow-up visit once written informed consent is provided. Participants from either the control group or intervention group 1 can be included in this study. Participants from the intervention group 2 are excluded to limit the number of groups and parameters in this exploratory study. Additional exclusion criteria are: use of systemic antibiotics in the 3 months prior to the first sampling visit, diagnosis with inflammatory bowel disease and prolonged institutionalisation (>4 weeks) in the 3 months prior to the first sampling visit. There is no restriction other than consent rate to the number of PROMISS participants that will be included in this side study.

Once all samples from all participants are collected, faecal samples are shipped to the Wallenberg Laboratory of Cardiovascular and Metabolic research (at the University of Gothenburg, in Sweden) for 16S ribosomal RNA (rRNA) sequencing using sequencing methods previously described.^80^ The tongue swabs will be sent to the Netherlands Organisation for Applied Scientific Research for 16S rRNA sequencing as is previously described.^81^

#### fMRI study

In the fMRI study, we will investigate the effect of personalised dietary advice aiming at increasing protein intake in community-dwelling older adults with lower habitual protein intake on central brain circuits involved in the regulation of appetite. Several studies demonstrated that increasing protein intake affects appetite^82^ and the gut microbiota.^83^ However, none have studied the effects on both simultaneously, or the interaction. An fMRI scan will be used to measure the brain responses to visual or actual food cues. Brain activity in response to food cues will also be related to (shifts) in the gut microbiota. Therefore, only participants from the microbiota side study can be included in this study, with additional exclusion criteria: being claustrophobic, being diagnosed with a mental disorder (eg, depression or addiction), being uncorrectable visually or hearing impaired, or having a contra-indication for MRI scans (eg, having a pacemaker). Up to 50 participants will be included in this side study. This side study will only be conducted at the Dutch study site.

Once written informed consent is provided, participants who are included in this side study will be asked to visit the Amsterdam University Medical Centre, location VUmc, for an fMRI scan two times during the study period: at baseline and at 6-month follow-up visit. Prior to the fMRI scan, additional salivary and blood samples will be collected for determination of additional nutritional and microbial biomarkers. The protocol for the fMRI experiments has been previously described.^84 85^

## Discussion

There is an ongoing discussion whether the EFSA RDA of 0.8 g protein/kg BW/day is sufficient for older adults and whether it should be increased to at least 1.0–1.2 g protein/kg BW/day to support muscle health and functioning. National guidelines of some European countries already increased their RDA, that is, the RDA of the German-speaking countries (D-A-CH) is increased to 1.0 g/kg BW/day,^86^ and the Nordic Nutrition Recommendation has increased their RDA to 1.2 g/kg BW/day.^87^ The PROMISS trial is the first RCT which will investigate the effect of personalised dietary advice aiming at increasing protein intake and the combined effect of personalised dietary advice aiming at increasing protein and the timing of protein intake in close proximity of usual physical activity, on change in physical functioning after 6 months among community-dwelling older adults (≥65 years) with a habitual protein intake of <1.0 g/kg aBW/day. The PROMISS trial will therefore provide additional insight to the question whether the current EFSA RDA for protein for older adults should be increased to 1.2 g/kg aBW/day, and whether optimal timing of protein intake will additionally benefit physical functioning.

A strong and unique aspect of the PROMISS trial is that we will include participants with a habitual protein intake <1.0 g/kg aBW/day, excluding those with a BMI <18.5 and >32.0 kg/m^2^. This will allow us to examine the effects of increasing protein intake from <1.0 to at least 1.2 g/kg aBW/day. An innovative component of our study is that we will investigate the combined benefit of increasing protein intake and timing of protein intake with usual physical activity on physical functioning and other health-related outcomes. Another strength is that in our study the intervention is based on personalised dietary advice which is likely more feasible in the long term to maintain in everyday life, compared with providing custom-prepared meals^19^ or protein supplements,^88 89^ as done in most other studies. Finally, we will be able to investigate the effect of persuasive technology on adherence to the dietary advice strategy, and the effect of the dietary advice on the microbiota composition and on central responses to food-cues in brain areas involved in appetite regulation. One limitation of this study is that the biological value of the total protein intake (ie, type of amino acids) is unknown. Another limitation is that the duration of the trial might not be long enough to observe a sufficient amount of incident cases of for example, risk of malnutrition, frailty or risk of sarcopenia.

In summary, this RCT will demonstrate the effectiveness of personalised dietary advice aiming at increasing protein intake to at least 1.2 g protein/kg BW/day on physical functioning in older adults with a lower habitual protein intake, with or without the advice to consume protein in close proximity of usual physical activity.

## Ethics and dissemination

The study has been approved by the Ethics Committee of the Helsinki University Central Hospital, Finland (ID of the approval: HUS/1530/2018) and The Medical Ethical Committee of the Amsterdam UMC, location VUmc, Amsterdam, the Netherlands (ID of the approval: 2018.399). Oral informed consent will be obtained from each participant before the screening procedure and written informed (please see online supplemental appendix 2) consent will be obtained from each participant before any measurement takes place. Personal data were not identifiable during the analysis.

10.1136/bmjopen-2020-040637.supp2Supplementary data

Results will be sent to national and international conferences and will submitted for publication in peer-reviewed journals. In addition, lay abstracts will be made available for participants and the public. Links to research output and dissemination activities will be made available on the PROMISS website, available at www.promiss-vu.eu and social media channels.
